### Sample size

2.2

We used change in bone mineral density (BMD) as the main effect indicator to estimate the sample size. Sample size calculations are performed to determine the number of participants necessary to detect effect sizes. Very few randomized controlled trials have examined the effect of TCC or CST on BMD in the elderly.

Based on similar previous studies^[19,20]^ and our preliminary experiment, the means with SDs of the BMD (lumbar spine) were X1 = 0.007 (SD1 = 0.098), X2 = 0.043 (SD2 = 0.108), X3 = 0.021 (SD3 = 0.0915), and X4 = 0.051 (SD4 = 0.099) in the CG, CST, TCC, and CTG, respectively. The sample sizes per group were calculated according to the formula: 

(i)with a type I error of 5% (α = 0.05) and 80% power (β = 0.10).(ii)K: groups, K = 4.(iii)Ψ: K = 4, V1 = K-1 = 3; V2 = N-1, N desirable maximum, Ψα, β, K-1,∞ = 2.17 (Obtained from statistical tables).(iv)X0 = (X1 + X2 + X3 + X4)/K = 0.0305.

We can calculate the number of samples as n≈80, considering a 20% dropout and exit rate. Thus, a minimum of 384 total participants is necessary to reach the target of 96 participants per group.

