### Participants and recruitment

2.3

We will recruit 384 eligible participants from the Ningxia Yuehai Service Center. The eligible elderly must meet the following inclusion criteria. A CONSORT diagram of participant recruitment is shown in Table 1. We intend to promote the recruitment programme through advertisements on community bulletin boards and community broadcasts. Researchers will register the interested participants for the first time and conduct a corresponding screening assessment. After baseline assessment, eligible participants will be randomly assigned to 1 of the 4 research groups.

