### Statistical analysis

2.13

We will use the intention-to-treat (ITT) analysis and per-protocol subject (PPS) analysis to analyze the primary and secondary outcomes. When there is a missing data, we will use the last observation carried forward method to deal with it. The continuous variables will be expressed as the mean ± SD. All categorical variables will be expressed in terms of their standard error. After examining whether the data accord with normality test (the Kolmogorov–Smirnov test), we will use ANOVA (assuming a normal distribution) or Kruskal–Wallis (a nonparametric test) to analyze the measurement results. We will use the Bonferroni method to appropriately adjust the overall level of significance for multiple outcomes.

For all the analyses of this study a significance level of 95% (two-sided *P* < .05) will be used. All statistical tests will be conducted using SPSS Statistical Software (IBM SPSS Statistics for Windows, Version 21.0. Armonk, NY).

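### A normality pre-test picks ANOVA or Kruskal–Wallis, the analysed scale (change or follow-up value) is not stated, and no baseline covariate enters although baseline is measured before randomisation.

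*Protocol article*

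**What the plan says.** Section 2.13 sets the outcome test by a rule: "After examining whether the data accord with normality test (the Kolmogorov–Smirnov test), we will use ANOVA" if the data look normal, and Kruskal–Wallis otherwise. It calls the analysed data only the measurement results. It does not say whether these are follow-up values or changes from baseline, and it names no covariate.

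Section 2.2 is more specific about the sizing endpoint: "We used change in bone mineral density (BMD) as the main effect indicator to estimate the sample size". Its inputs are means and SDs: "X1 = 0.007 (SD1 = 0.098), X2 = 0.043 (SD2 = 0.108), X3 = 0.021 (SD3 = 0.0915), and X4 = 0.051 (SD4 = 0.099".

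Baseline values exist for all participants. Sections 2.11 and 2.12.5 place the primary and secondary outcomes at baseline, and section 2.3 says: "After baseline assessment, eligible participants will be randomly assigned to 1 of the 4 research groups". Section 2.7 repeats that order.

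**The concern.** Two things are fixed badly.

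First, the data choose the test. ANOVA compares means. Kruskal–Wallis compares distributions through ranks, gives no estimate of a mean difference and takes no covariate. Primary BMD is measured at several sites, and step test, vital capacity, blood pressure and heart rate are also primary, so different primary outcomes could end up testing different hypotheses. If the gate sends BMD to Kruskal–Wallis, the test no longer matches a sample size built on means and SDs. With roughly 77 to 96 per group, inference on means is robust to moderate non-normality, so the gate buys little.

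Second, a baseline value measured before randomisation is a valid covariate that costs nothing, and the stated tests do not adjust for it. With the scale also left open, a reader cannot tell whether baseline enters by subtraction or not at all. At stake is precision in a trial whose own inputs leave little margin.

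**Working it through.** **Inputs.** From section 2.2: means 0.007, 0.043, 0.021, 0.051; SDs 0.098, 0.108, 0.0915, 0.099; "X0 = (X1 + X2 + X3 + X4)/K = 0.0305"; α = 0.05; 80 per group, raised to 96 for 20% dropout. Completers: 96 × 0.8 = 76.8, taken as 77. The baseline-to-follow-up correlation ρ is not in the document; I assume 0.5 to 0.95.

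**The plan's own figure.**
- Mean variance = (0.009604 + 0.011664 + 0.008372 + 0.009801)/4 = 0.009860.
- Σ(Xi − X0)² = 0.000552 + 0.000156 + 0.000090 + 0.000420 = 0.001219.
- The printed formula is missing from the text at hand. I assume the usual form for these symbols, n = Ψ² × mean variance / [Σ(Xi − X0)²/(K − 1)]. The ratio is 0.009860/(0.001219/3) = 24.27.
- With the stated Ψ ("2.17 (Obtained from statistical tables"), n = 2.17² × 24.27 = 114.3, not 80. That Ψ belongs to 90% power; 80% power needs 1.906, giving n = 88.2 (90 by exact F). The section states both powers at once: "with a type I error of 5% (α = 0.05) and 80% power (β = 0.10". So 80 is not reproduced. That is a separate error and serves here only as the starting point.

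**Power without adjustment.** The four-group F test has noncentrality λ = n × 0.001219/0.009860, with 3 and 4n − 4 degrees of freedom.

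| n per group | λ | Power |
|---|---|---|
| 77 | 9.52 | 73.2% |
| 80 | 9.89 | 75.0% |
| 96 | 11.87 | 83.2% |

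**Effect of adjusting for baseline.** Assume equal variance σ² at both visits and a common slope.
- Variance of a follow-up value: σ².
- Variance of a change: 2σ²(1 − ρ).
- ANCOVA residual variance: σ²(1 − ρ²).
- ANCOVA against change: (1 − ρ²)/[2(1 − ρ)] = (1 + ρ)/2.
- ANCOVA against follow-up values: 1 − ρ².

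| ρ | (1+ρ)/2 | 1−ρ² |
|---|---|---|
| 0.5 | 0.75 | 0.75 |
| 0.7 | 0.85 | 0.51 |
| 0.8 | 0.90 | 0.36 |
| 0.9 | 0.95 | 0.19 |
| 0.95 | 0.975 | 0.0975 |

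The variance saving is therefore 2.5–25% against ANOVA of change, and 25–90% against ANOVA of follow-up values.

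**Power with ANCOVA, taking the stated SDs as SDs of change.** Divide λ by (1 + ρ)/2 and use 4n − 5 error degrees of freedom.

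| ρ | 77 per group | 96 per group |
|---|---|---|
| none (ANOVA of change) | 73.2% | 83.2% |
| 0.95 | 74.4% | 84.2% |
| 0.9 | 75.6% | 85.2% |
| 0.8 | 78.1% | 87.2% |
| 0.7 | 80.6% | 89.2% |
| 0.5 | 85.7% | 92.9% |

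At 77 per group, 80% is reached at ρ = 0.7 but not at 0.8.

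**If instead the SDs are those of follow-up values and follow-up values are compared**, ANCOVA power at 77 per group is 86%, 96%, 99.5% and above 99.9% at ρ = 0.5, 0.7, 0.8 and 0.9.

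**The case against.** A reader might infer that the planned analysis ignores baseline altogether. The document does not establish that. Section 2.2 defines the sizing endpoint as a change, and an ANOVA of change uses baseline by subtraction. The large savings, up to 90%, apply only if raw follow-up values are compared, which section 2.13 neither says nor excludes.

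A reader might also infer that adjustment would cure the power shortfall. It would not do so reliably. On the change reading at ρ = 0.9 or above, power with 77 completers stays at 74–76%, and the shortfall comes from the sample-size calculation.

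The 73% is itself a completers-only figure. Section 2.13 plans an intention-to-treat analysis with last observation carried forward. With all 96 per group analysed, nominal power is 83%, although carrying baseline forward as a zero change may dilute the effect. That point stands, so both figures are shown.

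Two further points stand in part. Covariates are often left to an analysis plan, so silence on them alone would not be a finding; but this section names the tests and the rule for choosing between them, and ANCOVA would depart from it. A rank test can be run on changes and is reasonable for a skewed outcome such as pain VAS; that supports naming it in advance as a sensitivity analysis, not letting a pre-test choose it.

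**Conclusion.** The point holds in this form: section 2.13 lets a Kolmogorov–Smirnov test choose the outcome test, leaves the analysed scale unstated and includes no baseline covariate. The pre-test fault stands in the text and needs no assumption. In large samples ANCOVA is at least as precise as either ANOVA, so some precision is lost on both readings.

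The size of the loss depends on ρ, which the document does not give. On the change reading, which section 2.2 favours, the gain in power is about 1 to 13 percentage points at 77 per group and 1 to 10 at 96. The power figures take the plan's means and SDs at face value, use a single test at 0.05 and allow for no Bonferroni adjustment, which section 2.13 also plans. This is a worthwhile, cost-free improvement. It does not replace correcting the sample size.

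**What to change.** In section 2.13, and in the analysis plan if there is one:

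- For each continuous outcome, pre-specify an ANCOVA of the follow-up value at each visit where that outcome is measured, with arm and the baseline value of that outcome as terms.
- Report adjusted mean differences between arms with 95% confidence intervals.
- Remove the Kolmogorov–Smirnov gate.
- Keep rank-based tests as a named sensitivity analysis, for example for pain VAS.

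Stating the follow-up value as the response also settles the open question of scale. The cost is one paragraph, with no new data or participants, and the planned SPSS software can fit the model. The sample-size calculation in section 2.2 needs its own correction.

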## Abstract

**Background::**

According to the national census, China has gradually become an aging society; moreover, aging has become an irreversible worldwide trend in the twenty-first century. Aging can lead to decreased physical function, mobility, cardiopulmonary function and quality of life (QOL). The feasibility and benefits of core strength training (CST) and Tai Chi Chuan (TCC) in older adults (including improving cardiovascular, musculoskeletal, and mental health outcomes) have been confirmed in previous studies. To date, these exercise programmes have not been systematically compared, and the potential benefits of their combined use have not been tested. The primary objective of this **s**tudy protocol is to evaluate the effects of CST compared to those of TCC on the function of the musculoskeletal system and the cardiopulmonary system in older adults.

The second objective is to test the effectiveness of combined physical training that incorporates CST and TCC.

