**Discussion::**

The results of this study protocol are expected to clarify the synergistic effect of CST and TCC training on musculoskeletal and cardiopulmonary function in older adults. Furthermore, these findings will confirm whether combined or exclusive CST and TCC training, is more effective at improving functional outcomes in the elderly.

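### The trial is sized on a four-group omnibus test, but its primary objective is CST versus TCC, for which the plan's own BMD figures give only about 28–33% power

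*Protocol article*

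**What the plan says.** **Objectives.** The Abstract (Background) gives the primary objective as to "evaluate the effects of CST compared to those of TCC on the function of the musculoskeletal system and the cardiopulmonary system in older adults". It continues: "The second objective is to test the effectiveness of combined physical training that incorporates CST and TCC". The Introduction repeats both aims. The Abstract (Discussion) says that "these findings will confirm whether combined or exclusive CST and TCC training, is more effective at improving functional outcomes in the elderly", and section 3.1 closes in similar terms.

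**Sizing (2.2).** "We used change in bone mineral density (BMD) as the main effect indicator to estimate the sample size". The planning values for lumbar-spine BMD are "X1 = 0.007 (SD1 = 0.098), X2 = 0.043 (SD2 = 0.108") for control (CG) and CST, and "X3 = 0.021 (SD3 = 0.0915), and X4 = 0.051 (SD4 = 0.099") for TCC and the combined group (CTG). The calculation uses K = 4 groups, V1 = K−1 = 3, a tabulated Ψ of 2.17 and a grand mean of 0.0305, "with a type I error of 5% (α = 0.05) and 80% power (β = 0.10"). It arrives at about 80 per group, raised to 96 per group (384 in total) for 20% dropout.

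**Analysis (2.13).** For the measurements, "we will use ANOVA (assuming a normal distribution) or Kruskal–Wallis (a nonparametric test) to analyze the measurement results". Bonferroni adjustment is mentioned for multiple outcomes; nothing is said about comparisons between groups. No section gives power for any pair of arms.

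**The concern.** The primary objective concerns one pair of arms. A calculation with three numerator degrees of freedom and deviations from a grand mean asks instead whether any of the four means differ. The two questions can have different answers. Under the planning means the largest gap is combined versus control (0.044), twice the CST−TCC gap (0.022), so a significant F-test may say nothing about CST versus TCC.

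Two misreadings are at stake. A significant omnibus result could be taken as support for one training over the other. A non-significant CST−TCC comparison could be taken as showing the two are alike, when the trial had little chance of separating them. A reader who sees 80% power next to this primary objective would be falsely reassured.

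**Working it through.** **Inputs (section 2.2).** Means: CG 0.007, CST 0.043, TCC 0.021, CTG 0.051. SDs: 0.098, 0.108, 0.0915, 0.099. Two-sided α = 0.05 (2.13). I use three sizes per group: 80 (the plan's figure before dropout), 96 (all randomised) and 77 (96 × 0.8 = 76.8).

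**Step 1: the plan's own figure.**
- Grand mean = (0.007 + 0.043 + 0.021 + 0.051)/4 = 0.0305, which agrees with 2.2.
- Mean variance = (0.098² + 0.108² + 0.0915² + 0.099²)/4 = 0.00986, so the pooled SD is 0.0993.
- Between-group sum of squares = 0.0235² + 0.0125² + 0.0095² + 0.0205² = 0.001219.
- The formula is not visible in the text. The standard one is n = Ψ² × mean variance / [sum of squares/(K−1)]. With Ψ = 2.17 this gives 4.709 × 0.00986/0.000406 ≈ 114. With Ψ = 1.91, the value matching 80% power, it gives about 89. Neither is 80.
- Exact omnibus power (noncentral F, λ = n × 0.001219/0.00986, df 3 and 4(n−1)): λ = 9.89 and power 75% at 80 per group; λ = 11.87 and power 83% at 96.

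**Step 2: pairwise power.** SE = 0.0993 × √(2/n), which is 0.0160 at 77, 0.0157 at 80 and 0.0143 at 96. Power is from the noncentral t with 4(n−1) df and noncentrality difference/SE. For CST−TCC at 80 this is 0.022/0.0157 = 1.40.

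| Contrast | Difference | 77 per group | 80 per group | 96 per group |
|---|---|---|---|---|
| CST−TCC | 0.043 − 0.021 = 0.022 | 28% | 29% | 33% |
| CTG−TCC | 0.051 − 0.021 = 0.030 | 46% | 48% | 55% |
| CTG−CST | 0.051 − 0.043 = 0.008 | 8% | 8% | 9% |
| CTG−CG | 0.051 − 0.007 = 0.044 | 78% | 80% | 86% |

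Using only the CST and TCC SDs (0.1001) gives 28% at 80 per group. Reaching 80% power for CST−TCC would take about 321 per group with the pooled SD, or 325 with the two-arm SD.

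**Step 3: precision of CST−TCC.** The 95% CI half-width is t × SE: 1.967 × 0.0157 = ±0.031 at 80 per group and 1.966 × 0.0143 = ±0.028 at 96. Both exceed the assumed difference of 0.022.

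**Step 4: can the omnibus test stand in for the contrast?** Set CST and TCC both to their average, 0.032, and leave the other two means alone. The sum of squares falls from 0.001219 to 0.000977. At 80 per group λ = 7.93 and the F-test still has 64% power, against 75% under the stated means. The CST−TCC gap contributes only 0.022²/2 = 0.000242, about 20% of the sum of squares.

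**The case against.** **A separate analysis plan may name the contrasts.** ANOVA is also the model from which contrasts are taken, and section 2.13 does not exclude them. This stands: the absence of named post hoc tests is not, alone, the finding. But the objective and the sizing basis are both stated here and do not match, and naming the contrast elsewhere would not raise its power.

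**The low figure depends on n.** Section 2.13 specifies intention-to-treat with last observation carried forward, and 2.14 seeks a final evaluation before withdrawal, so the analysed number could approach 96. This also stands, which is why the range runs to 33%. The conclusion does not change.

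**The second objective is partly served.** Its wording covers combined versus control, which has 80–86% power at 80–96 per group. That is fair. The comparison of combined with single training, which the Abstract also promises to settle, has 8–9% (versus CST) and 48–55% (versus TCC).

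**Stronger readings to avoid.** A reader might infer that a significant omnibus test is the trial's success criterion. No section defines one; the omnibus test is simply the only between-group test stated. Nor does the 28% apply to the primary outcomes in general: it is for lumbar-spine BMD, and the plan gives no planning figures for step test, vital capacity, blood pressure or heart rate.

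**Conclusion.** The mismatch is real and should be corrected. The trial names CST versus TCC as primary, yet it is sized on a test that would be significant about 64% of the time at 80 per group even with no difference between those two arms. For lumbar-spine BMD, CST−TCC power is about 28–33% over 77 to 96 per group, so a true difference of the assumed size would be missed roughly seven times in ten.

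This rests on the plan's own means and SDs, a common SD, equal groups and an unadjusted two-sided 0.05. Any adjustment lowers it further. At 0.05/3, for example, the power at 80 per group is about 16%, and the Bonferroni adjustment for outcomes in 2.13 would have a similar effect if BMD shares its significance level with other outcomes.

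The 80% in 2.2 should not simply be relabelled as omnibus power. At 80 per group that power is about 75%, and the stated β = 0.10 would mean 90%.

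**What to change.** **Section 2.13.** Name CST−TCC as the primary contrast, taken from the four-group model, tested at two-sided 0.05 and reported with a 95% CI. Say how that level relates to the Bonferroni adjustment for outcomes. Name CTG−CST, CTG−TCC and CTG−CG as a separate secondary family with Holm adjustment, so that CST−TCC is clearly outside it. Treat the omnibus test as supportive. These contrasts do not test synergy in the sense of a more-than-additive effect, so they should not be described as doing so.

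**Section 2.2.** State that the calculation is for the omnibus test. Replace the contradictory power and β statement with the recomputed power, about 75% at 80 per group and 83% at 96. Add that CST−TCC power on lumbar-spine BMD is about 28–33%, with an expected 95% CI half-width of about ±0.028 to ±0.031, and that no planning figures support the cardiopulmonary outcomes.

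**Abstract (Discussion) and 3.1.** Temper the promise to confirm which training is more effective; estimating the differences is what this size can support.

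**Cost.** The stated power for the primary question becomes visibly less favourable. No participants or procedures are added.

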#### Bone mineral density (BMD)

2.12.1

We will assign a professional technician to perform standard BMD measurements by using DXA (GE Lunar iDXA with encore 12.0 software, GE Healthcare Lunar, Madison, WI).^[22]^ BMD measurements includes the whole body, lumbar spine (L1-L4), proximal femur of the left leg, and left fore-arm.^[23]^ In order to ensure the accuracy of the collected data, all instruments should be calibrated by the inspector before the measurement is carried out.

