#### Cardiopulmonary function

2.12.2

Cardiopulmonary function in this study will be evaluated by step test, vital capacity, blood pressure and heart rate. The step test will be carried out using a step tester (product type: CSTF-TZ-5000) manufactured by Beijing Titanium Oriental Co., Ltd. The vital capacity was measured using a vital capacity tester (product type: CSTF-FH-5000) produced by Beijing Zhongtai Oriental Co., Ltd. Blood pressure and resting heart rate will be tested by an electric sphygmomanometer produced by Omron, Dalian, China (product type: HEM-76C).

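### The trial is sized on lumbar spine BMD at α = 0.05, but the Bonferroni rule over several primary outcomes would test it at a smaller α, where the stated 80% power is not reached

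*Protocol article*

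**What the plan says.** Three parts of the protocol article bear on the α for the primary analysis.

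- **Section 2.2, Sample size.** "We used change in bone mineral density (BMD) as the main effect indicator to estimate the sample size". The planning values are for the lumbar spine, and the error rates are given as "with a type I error of 5% (α = 0.05) and 80% power (β = 0.10". The result is about 80 per group, raised to 96 per group (384 in all) for 20% dropout. No allowance for multiple outcomes is mentioned.
- **Section 2.12, Primary outcomes.** Two domains appear under this heading. For the first: "BMD measurements includes the whole body, lumbar spine (L1-L4), proximal femur of the left leg, and left fore-arm". For the second: "Cardiopulmonary function in this study will be evaluated by step test, vital capacity, blood pressure and heart rate". No measure is singled out. Sections 2.10 and 2.12.5 add that primary measurement is repeated at the end of follow-up (25 weeks).
- **Section 2.13, Statistical analysis.** "We will use the Bonferroni method to appropriately adjust the overall level of significance for multiple outcomes". The section names neither the outcomes in the family nor the divisor. It then sets the level with "For all the analyses of this study a significance level of 95"%, glossed as two-sided P < .05.

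**The concern.** A sample size calculation supports a power claim only if it uses the α of the test that will be run. Here the calculation uses 0.05 for one outcome, while the analysis section promises to divide α over several. If lumbar BMD is one member of the Bonferroni family, its threshold is 0.05 divided by the family size, and the power in section 2.2 describes a test that will not be carried out.

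Two things are at stake. The stated power overstates the chance of detecting the planned effect on the outcome used for sizing. And because the divisor is open, a lumbar BMD result with P somewhat below 0.05 could be called positive or negative depending on a choice made after the data are seen. An analysis plan written later can settle the divisor, but it cannot restore the power without a change in sample size.

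**Working it through.** **Inputs (section 2.2).** Control and CST: "X1 = 0.007 (SD1 = 0.098), X2 = 0.043 (SD2 = 0.108"). TCC and combined: "X3 = 0.021 (SD3 = 0.0915), and X4 = 0.051 (SD4 = 0.099"). K = 4 groups, Ψ = 2.17, equal allocation, about 80 per group evaluable, 96 per group recruited.

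**Step 1: effect and variance.**
- Grand mean: (0.007 + 0.043 + 0.021 + 0.051)/4 = 0.0305, as in the plan.
- Sum of squared deviations: 0.0235² + 0.0125² + 0.0095² + 0.0205² = 0.001219.
- Mean variance: (0.098² + 0.108² + 0.0915² + 0.099²)/4 = 0.0098603.
- Ratio: 0.001219/0.0098603 = 0.12363. Cohen's f = √(0.12363/4) = 0.176.

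**Step 2: the plan's own figure.** The formula itself is not legible in the text. I assume the usual multi-group form, n = Ψ² × (ΣSD²/K) / (Σ(Xi − X0)²/(K − 1)).
- Ψ = 2.17, which corresponds to β = 0.10: 4.7089 × 0.0098603/0.00040633 = 114.3 per group.
- Ψ = 1.91, which corresponds to β = 0.20: 3.6481 × 0.0098603/0.00040633 = 88.5, so 89 per group.
- Exact F test: 90 per group for 80% power, 116 for 90%.

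The stated figure of about 80 is not reproduced on either reading of β. That is a separate defect. It matters here because the starting power at 80 per group is already below 80%, and the loss due to Bonferroni must be measured from that lower base.

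**Step 3: power of the four-group test at the Bonferroni α.** One-way ANOVA, non-central F with 3 and 4(n − 1) degrees of freedom and non-centrality n × 0.12363 (9.89 at n = 80, 11.87 at n = 96).

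| Assumed family | α per test | Power, n = 80 | Power, n = 96 | n per group for 80% |
|---|---|---|---|---|
| Lumbar BMD only | 0.05 | 75% | 83% | 90 |
| Two domains | 0.05/2 = 0.025 | 65% | 75% | 106 |
| Eight measures | 0.05/8 = 0.00625 | 46% | 58% | 137 |
| Nine measures | 0.05/9 = 0.00556 | 45% | 56% | 140 |

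Eight is four BMD sites plus four cardiopulmonary measures. Nine counts systolic and diastolic pressure separately. The n = 96 column is for the case in which everyone randomised is analysed by intention to treat with the last observation carried forward, and the planned differences persist in full.

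Power falls as the divisor grows. The two-domain row is therefore the best case once any division is made, and it is below 80% in both columns. The 106 evaluable per group that it needs exceeds the 96 to be recruited.

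**Step 4: the other reading of the .05 sentence.** If every measure were tested at an unadjusted 0.05, family-wise error with all nulls true and independent tests would be 1 − 0.95² = 10% for two tests, 1 − 0.95⁸ = 34% for eight and 1 − 0.95⁹ = 37% for nine. Positive correlation between the measures would lower these figures.

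**The case against.** A reader might infer that section 2.13 contradicts itself, by promising Bonferroni and then using P < .05 throughout. The text does not establish this. The two sentences agree if .05 is the family-wise level, or if Bonferroni-adjusted P values are compared with .05. The wording is ambiguous, and the family-wise error of about one third arises only on the reading that ignores the Bonferroni sentence, and then only as far as the tests are independent.

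A reader might also infer that power falls below one half under the plan as written. That requires a divisor of eight or more and about 80 evaluable per group. The document gives no divisor. A family of two domains is a fair reading of section 2.12, and with 96 per group power stays above one half even for nine measures. Counting the 25-week measurements as further members of the family would be one more assumption.

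The strongest defence is that lumbar BMD is in effect the single primary outcome: section 2.2 treats BMD as the main indicator, and section 2.12.5 uses the singular when it describes the 25-week measurement. Then 0.05 would be the right α. But section 2.12 lists both domains as primary without ranking them, section 2.10 uses the plural, and nothing exempts lumbar BMD from the adjustment. A separate analysis plan could define the family, so its absence here is not the fault. The mismatch between two things that are stated, the sizing α and the Bonferroni rule, remains.

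**Conclusion.** The point holds as a mismatch between sections 2.2 and 2.13. With lumbar BMD in a Bonferroni family, the α used for sizing is not the α at which it will be tested, and the stated 80% power is not reached for any divisor of two or more. At 80 per group the drop is from 75% to 65% for two domains, 46% for eight measures and 45% for nine. At 96 per group it is from 83% to 75%, 58% and 56%. These figures rest on the plan's own means and SDs, a four-group omnibus test, and a family size that the reader must assume, so they are a range. Part of the gap to 80% at n = 80 comes from the sizing itself and not from Bonferroni. The .05 sentence needs clarifying but is not shown to be a contradiction.

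**What to change.** In section 2.13, state which primary measures and which time point form the Bonferroni family, and that .05 is the family-wise level (or that it applies to Bonferroni-adjusted P values). In section 2.2, restate the power for lumbar BMD at the resulting per-test α.

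This costs a few sentences, plus the admission that power is lower than stated. Holding 80% instead would need 106 evaluable per group for two domains or 137 for eight measures, before dropout.

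The sponsor could instead name lumbar spine BMD change at the end of the intervention as the single primary outcome at 0.05. That removes the mismatch, but it makes the cardiopulmonary outcomes secondary although the stated aims cover both systems, and power would still be about 75% at 80 per group.

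### Section 2.13 names single-step Bonferroni for the multiple outcomes, which is valid; Holm's step-down version is a cheap improvement that never rejects fewer outcomes at the same family-wise error

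*Protocol article*

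**What the plan says.** Section 2.13 fixes the multiplicity method by name: "We will use the Bonferroni method to appropriately adjust the overall level of significance for multiple outcomes". Each outcome is compared across the four groups with a single overall test: "we will use ANOVA (assuming a normal distribution) or Kruskal–Wallis (a nonparametric test) to analyze the measurement results". The working level is two-sided 0.05.

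The article does not list the outcomes in the adjusted family. Section 2.12 places two groups of measures under primary outcomes:

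- Section 2.12.1: "BMD measurements includes the whole body, lumbar spine (L1-L4), proximal femur of the left leg, and left fore-arm".
- Section 2.12.2: "Cardiopulmonary function in this study will be evaluated by step test, vital capacity, blood pressure and heart rate".

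Counting blood pressure once, that makes four BMD sites and four cardiopulmonary measures.

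The sample size in section 2.2 rests on one of these: "We used change in bone mineral density (BMD) as the main effect indicator to estimate the sample size". The means and SDs given there are for the lumbar spine, and alpha is an unadjusted 0.05.

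**The concern.** Single-step Bonferroni tests each of m outcomes at 0.05/m, however many of the others have already been rejected. Holm tests the smallest P value at 0.05/m, the next at 0.05/(m − 1), and so on, and stops at the first failure. Both hold the family-wise error at 5% whatever the dependence between outcomes. Every Holm threshold is at least as large as the Bonferroni threshold, so Holm cannot lose a rejection that Bonferroni makes.

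This matters most when several outcomes respond together. The trial asks about musculoskeletal and cardiopulmonary function jointly, and whole-body BMD includes the regions measured separately, so several responding outcomes are plausible. At stake is some power for the second and later outcomes. No false-positive risk is involved.

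**Working it through.** **Inputs from section 2.2.** Means 0.007, 0.043, 0.021, 0.051; SDs 0.098, 0.108, 0.0915, 0.099; 96 per group; 20% dropout.

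**Assumptions not in the article.** The family has m = 8 outcomes. Each affected measure carries the same standardised effect as lumbar-spine BMD. Correlation between outcomes is 0 or 0.5. Completers per arm are 96 × 0.8 = 76.8, taken as 77.

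**The plan's own figure first.**

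- Grand mean = 0.122/4 = 0.0305, as printed.
- Sum of squared deviations = 0.00055225 + 0.00015625 + 0.00009025 + 0.00042025 = 0.001219.
- Mean variance = (0.009604 + 0.011664 + 0.00837225 + 0.009801)/4 = 0.0098603, so the pooled SD is 0.0993.
- The formula itself is not legible in the text. The usual one for these inputs is n = Ψ² × mean variance ÷ [sum of squares/(K − 1)]. With Ψ = 2.17 it gives 4.7089 × 0.0098603 ÷ 0.00040633 = 114 per group.
- The Ψ value for 80% power, 1.906, gives 88.

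The stated 80 is not reproduced. That is a separate matter, but it shows that power is not generous before any multiplicity adjustment.

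**Power for one affected measure at n = 77.** Noncentrality = 77 × 0.001219/0.0098603 = 9.52, on 3 and 4 × 77 − 4 = 304 degrees of freedom. Noncentral-F power is 73% at 0.05 and 44% at 0.05/8 = 0.00625. The large-sample chi-square approximation gives 45% at 0.00625, which is why simulated values sit at 44–45%.

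**Thresholds for m = 8.** Bonferroni uses 0.00625 throughout. Holm uses 0.00625, 0.00714, 0.00833, 0.0100, 0.0125, 0.0167, 0.025 and 0.05 in order. The first threshold is the same, so the chance of at least one rejection must be the same.

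**Simulation** (40,000 runs per case, 3-degree-of-freedom overall tests, chi-square approximation). Where two values are given, they are for correlation 0 and 0.5.

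| Measures affected (of 8) | Average power per affected measure, Bonferroni | Same, Holm | At least one rejection, both methods |
|---|---|---|---|
| 8 | 45% | 54% / 55% | 99% / 87% |
| 4 | 45% | 48% | 91% / 77% |
| 2 | 45% | 46% | 71% / 63% |
| 1 | 45% | 45% | 48% / 47% |

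In no run did Bonferroni reject an outcome that Holm did not. In the cases with unaffected measures, the family-wise error stayed below 5% for both methods.

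**Other family sizes** (n = 80, correlation 0.3, all effects real; Bonferroni then Holm): m = 2, 66% and 72%; m = 5, 54% and 64%; m = 9, 46% and 56%. With one real effect the gain was at most 0.2 points at each size.

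**The case against.** The strongest reply is that nothing here is wrong. Bonferroni is valid, prespecified and conservative, the article never claims that it is the most powerful option, and the same suggestion could be made to any trial that uses it. That stands, and it is why the point is an optional improvement.

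A reader might infer that power is being given away for nothing. The article does not support that. Single-step Bonferroni comes with simple matching simultaneous intervals. Under Holm an outcome can be declared significant while its Bonferroni interval includes the null. Section 2.13 plans no simultaneous intervals, so the cost is small, but it is not zero.

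A reader might also infer that real effects will be missed because of this choice. That is too certain. A later outcome is recovered only if its P value falls between the two thresholds and all smaller P values have passed theirs.

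The size of the gain also rests on assumptions. The article gives an effect for lumbar-spine BMD only, and nothing in it shows that blood pressure or vital capacity would respond to the same degree. The family of eight is assumed. The largest gain needs all eight to respond, and no stated objective requires success on every measure.

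One reply does not stand: that this belongs to an unseen analysis plan. The family could be listed there, but the article itself fixes the procedure by name.

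**Conclusion.** The point holds as a low-cost improvement, of minor importance. For hypothesis testing, Holm is never worse than the method named in 2.13 and is sometimes better, for any family of two or more outcomes and any dependence between them. That part needs no assumption.

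The size does. With eight measures, 77 per arm and the lumbar-spine BMD effect on every affected measure, the gain in average power per affected measure is about 9 to 10 percentage points if all eight respond, about 3 if four do, about 1 if two do, and none if one does. The probability of at least one significant outcome does not move.

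The text does not support calling the use of Bonferroni a mistake. Nor would Holm cure the limited power that follows from section 2.2, where the stated inputs do not lead to 80 per group.

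**What to change.** In section 2.13, replace *the Bonferroni method* with *the Holm step-down Bonferroni procedure*, applied to the declared outcome family, and state that Holm-adjusted P values will be reported. Make the change before the allocation codes are opened.

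The cost is one line of text and a short calculation. Sort the m P values from the SPSS output, multiply the smallest by m, the next by m − 1 and so on, carry forward the running maximum, and cap at 1. If intervals are shown, say whether they are unadjusted or Bonferroni-adjusted, and note that a Bonferroni interval may include the null for an outcome that Holm declares significant. The sample-size calculation in section 2.2 needs its own correction.
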